9.5.2 Secondary Outcome

For the secondary outcomes, similar mixed models will be used. Again the feasibility of such analysis for each outcome will be checked during the blind review and a detailed analysis plan for the secondary outcome will be proposed in the final statistical analysis plan.

### 9.5.1 Management of subject withdrawal

Sample size is adjusted to account for a possible 10% drop out rate. Thus, 66 subjects need to be recruited.

### 9.5.2 Intention to treat analysis

Data from all randomized subjects will be considered in the intention to treat model (for the primary outcome).

### 9.5.3 Per protocol analysis

Per protocol, evaluation will exclude data from subjects in the following conditions:

- Prohibited concomitant treatment
- Subjects without the primary outcome available for Decaffeinated coffee and placebo
- Major violation of inclusion / exclusion criteria

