# OBJECTIVES OF THE TRIAL

## 3.1 Main objective

The primary objective is to evaluate whether an acute dose of CGA improves cognitive function and mood in healthy older adults.

Cognitive function will be assessed with a battery of standard validated behavioural cognitive tests. Cognitive functions assessed will be attention, working memory, emotional attention, information processing speed, and reaction time performance.

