## 4.2 Subjects, groups and centres

The number of subjects to complete the study protocol will be 58 (see 9.3 statistical section). All subjects will complete the 3 treatment conditions. Subject recruitment will be 66 to provide for a 10% drop-out rate.

The study will be a single-centred study, where all data will be collected at the Brain Sciences Institute, Swinburne University, Melbourne, Australia.

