# Statistical aspects and considerations

## 9.1 Background

The primary objective suggested for this trial is to evaluate the effect of acute CGA on attention in terms of performance on the Rapid Visual Information Processing (RVIP) task. In particular, the Total Number of correct Hits, the Reaction Time for the Correct Hits and the False Alarm Rate have been specified. We use the data from a previous trial (08.17.NRC) to estimate the effect sizes and to calculate the sample size needed to have 80% power to detect these effects. In particular, we use the 08.17.NRC data from the Placebo and Decaffeinated Coffee from Green Beans (which is abundant in CGA). The RVIP task consists of identifying targets (sets of 3 consecutive odd/even numbers) out of 96 possible targets. Thus theoretically speaking, this is a binomial trial for each subject with size=96. The success rate is estimated (using data from the placebo group in Trail 08.17.NRC) to be p = 63/96 = .656 which is moderate to large. Thus we expect the data to be fairly Normally distributed. A mixed analysis of covariance (ANCOVA) model was fit to the placebo and decaf coffee from green beans data from the 08.17.NRC trial. The normality and homoscedasticity assumptions were checked. The estimated effect size was an increased score of 2.45 points on the RVIP as compared to placebo and the with-in standard deviation was estimated to be 6.52.

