## Effects to be estimated

### 9.2.1 Primary Endpoint:

RVIP accuracy score

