### 9.2.2 Secondary Endpoint:

The secondary endpoints concerned are:

- Inspection Time – time that target is correctly identified in 80% of trials
- Serial Sevens - total number of subtractions and number of errors
- Serial Threes - total number of subtractions and number of errors
- Emotional face recognition task – percent of correctly recognised emotions
- N-back task - speed and accuracy
- Reaction Time – mean reaction time (ms)
- Bond and Lader Visual Analogue Scales
- Caffeine Research Visual Analogue Scales
- Brain doppler blood flow - mean velocity

Same comparison as primary objective on secondary outcomes:

Assess the effect of CGA vs. placebo on secondary outcomes.

Other comparisons of interest:

Assess the effect of CGA vs. decaffeinated coffee on primary and secondary outcomes.

Assess the effect of decaffeinated coffee vs. placebo on primary and secondary outcomes.

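### The per-protocol rule checks for decaffeinated coffee and placebo data although the primary comparison is CGA versus placebo; the effect is small and confined to a supportive analysis

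*Protocol*

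**What the plan says.** Section 3.1 states the aim: "The primary objective is to evaluate whether an acute dose of CGA improves cognitive function and mood in healthy older adults". Section 9.1 repeats it for the statistical part: "The primary objective suggested for this trial is to evaluate the effect of acute CGA on attention". Section 9.2.1 gives the primary endpoint as "RVIP accuracy score".

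Section 9.2.2 identifies the primary contrast indirectly. Under the line "Same comparison as primary objective on secondary outcomes" it writes "Assess the effect of CGA vs. placebo on secondary outcomes". Among the further comparisons it then lists "Assess the effect of decaffeinated coffee vs. placebo on primary and secondary outcomes". Section 3.2 likewise places replication of the decaffeinated coffee effect among the secondary objectives.

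Section 9.5.3 defines the per-protocol evaluation by three exclusions. The one that concerns data availability is "Subjects without the primary outcome available for Decaffeinated coffee and placebo". CGA does not appear in it. The section on intention to treat (9.5.2) keeps every randomized subject in that model for the primary outcome.

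**The concern.** A per-protocol analysis of the primary question should be defined by whether the two products being compared were observed. Here availability is tied to one product of the primary contrast (placebo) and to one product outside it (decaffeinated coffee). The product whose effect is the primary objective plays no part.

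Taken literally, the rule can discard subjects who hold exactly the pair of results that the primary comparison needs, and keep subjects who have no CGA result. At stake is whether the per-protocol result can serve as a clean check on the primary conclusion. Nothing in the protocol explains the choice or restricts the per-protocol analysis to the decaffeinated coffee comparison.

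**Working it through.** **1. The plan's own figures.** Section 9.1 gives an effect of 2.45 RVIP points, a within-subject standard deviation of 6.52 and 80% power. Section 9.3 gives 58 subjects, with 66 enrolled. The significance level is not stated; two-sided 0.05 is assumed here.

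- Normal approximation: (6.52 × (1.960 + 0.842) / 2.45)² = 55.6, so 56.
- Paired t-test with the noncentral t distribution, taking 6.52 as the standard deviation of the paired difference: n = 58, power 80.3%. The stated 58 is reproduced.
- Dropout: 58 / 0.90 = 64.4, so 65. The stated 66 is close and equals 6 × 11, a multiple of the six sequences of a three-treatment Williams design.
- Losses allowed for: 66 − 58 = 8.

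**2. What the rule does to each pattern of available RVIP results.** The bullet can be read in two ways: both values are required (the natural reading), or a subject goes only if both are missing.

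| RVIP available for | Both required | Excluded only if both missing | Within-subject CGA-placebo contrast |
|---|---|---|---|
| All three products | kept | kept | yes |
| CGA and placebo | **excluded** | kept | yes |
| Decaffeinated coffee and placebo | **kept** | **kept** | no |
| CGA and decaffeinated coffee | excluded | **kept** | no |
| CGA only | excluded | excluded | no |
| Decaffeinated coffee only, or placebo only | excluded | **kept** | no |

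Bold marks a classification that does not suit the primary contrast. On the natural reading, two of the three patterns with a single missing session are misclassified. On the other reading the wrongful exclusion disappears, but subjects without CGA are still kept, and so are subjects missing only placebo. On neither reading does a missing CGA result by itself lead to exclusion.

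**3. How many subjects (natural reading).** In a balanced six-sequence design, a subject who stops after two periods has seen CGA and placebo, decaffeinated coffee and placebo, or CGA and decaffeinated coffee, with probability 1/3 each. With k subjects missing exactly one session, k/3 are wrongly excluded and k/3 wrongly kept:

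- k = 8 (all allowed losses): 8/3 = 2.7 each
- k = 4: 4/3 = 1.3 each
- k = 2: 2/3 = 0.7 each

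Subjects who leave before or after the first test session have at most one product. They are excluded whether the rule names decaffeinated coffee or CGA, so k = 8 is a ceiling.

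**4. Effect on precision at the ceiling.** The CGA-placebo pairs in the per-protocol set are 58 under the rule as written and 58 + 2.7 = 60.7 if it named CGA and placebo. On the basis used in step 1, power is 80.3% at 58 pairs, 81.7% at 60 and 82.3% at 61. The difference is therefore about 80% against 82%.

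**The case against.** The strongest counter-argument is that very little depends on this bullet. The intention-to-treat model contains all randomized subjects, and section 4.2 plans that "All subjects will complete the 3 treatment conditions". Every subject who does so passes the availability rule under either wording. That stands, and it limits the weight of the point.

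Second, the planned model is a mixed ANCOVA with a random subject intercept, not an analysis of complete pairs. A subject without CGA still informs the placebo mean, the time effect, the baseline slope and the variance components, and is fully evaluable for decaffeinated coffee versus placebo. That also stands. A reader might infer that keeping such subjects biases the CGA estimate; the documents give no ground for this. What these subjects lack is a within-subject CGA-placebo contrast.

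Third, the wrongful exclusion depends on reading the bullet as requiring both values. That is the more natural reading but not the only one. The retention of subjects without CGA holds on both.

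Two further defences do not carry. The sample size was derived from placebo and green-bean decaffeinated coffee data of the previous trial, but section 9.1 uses these only as inputs and in the same paragraph names CGA as the object of the trial. The blind review described under Primary Outcome (9.5.1) may update the analysis plan, but it covers feasibility of the model, transformations and non-parametric methods and does not mention the analysis sets. Nor is this a detail left to an analysis plan: the protocol states a rule, and the rule conflicts with its own primary contrast.

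**Conclusion.** The bullet is wrong as written: its availability criterion does not match the primary comparison, and no section accounts for the difference. The size is small. At most about 2.7 subjects are wrongly excluded and 2.7 wrongly kept, assuming that all 8 allowed losses miss exactly one session and that each product is equally likely to be the one missed. The protocol gives no timing of dropout, so the plausible number is lower. The power figures also assume two-sided 0.05 and that 6.52 acts as the standard deviation of the paired difference.

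A reader might infer that the supportive analysis is run in the wrong population, or that nearly every incomplete subject is misclassified. The documents support neither. The planned 58 completers are classified identically under both wordings, and misclassification on the natural reading is confined to subjects who miss exactly one session, and that session is CGA or decaffeinated coffee. The case for a change rests on a set defined by the wrong contrast, not on lost power. This is a lower-level correction and does not threaten the primary conclusion.

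**What to change.** Before code breaking, reword the bullet in section 9.5.3 so that, for the primary comparison, a subject is excluded if RVIP accuracy is missing for CGA or for placebo. Writing **or** also removes the ambiguity of the present wording.

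For the other comparisons, either apply the same rule to the two products compared, or use one per-protocol set that requires all three products. Both are acceptable; the protocol should say which.

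The cost is one line of text. Sample size, randomization and conduct do not change. Timing matters, because a change to an analysis set after unblinding would look driven by the data.

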### 9.5.4 Interim analysis

None needed.

# Handling of adverse events

## 10.1 Definition of adverse events

The adverse event is defined as any untoward occurrence in a patient or clinical investigation subject administered an investigational product and which does not necessarily have to have a causal relationship with this treatment.

Adverse events are illnesses, signs or symptoms occurring or worsening, and/or abnormal laboratory findings during the course of the study. Adverse events include occasions when the subjects contact the investigator or their private physician and are examined or given medical direction. They may or may not lead to the withdrawal of the subject from the study.

Adverse events are generally classified as serious or non-serious. See Appendix 5 for classification system.

## 10.2 Reporting and documentation of adverse events

All adverse events occurring during the study will be reported and recorded whether or not they are considered to be non-serious, serious and/or related to the treatment. The following information will be required in each case:

- Subject and date
- Description of event
- Duration
- Frequency
- Intensity
- Seriousness
- Action taken
- Outcome and sequelae
- Relationship to test product

Definitions are included in Appendix 5.

Documentation of all adverse events includes completion of the appropriate section of the case report form (AE).

Documentation of a serious adverse event requires that a separate form (SAE) be completed by the investigators in each case (see Appendix 5).

In addition, the sponsor (via the Project Leader) will be notified by the investigator of serious adverse events. Such events should be reported immediately by phone and followed by a faxed SAE form within 24 hours.

## 10.3 Follow-up

If further information examinations are required to assess the relationship between an adverse event and treatment following the occurrence of the adverse event, all examinations or laboratory findings must be noted with their results in the CRF (section UV) or attached to a follow up file.

# Legal and ethical prerequisites

## 11.1 Legal requirements

Trial will be conducted according to the ICH-guidelines of Good Clinical Practice (GCP) set out by the Swinburne University Research Ethics Committee and the Therapeutics Goods Administration (TGA).

## Ethical aspects

### 11.2.1 Protection of the subject’s confidentiality

Confidentiality of all study participants will be maintained; codes for subject identification will be utilized.

### Informed consent

When the investigator has determined that the subject is an appropriate candidate for the study, the study will be described and explained orally to the subject. The investigator will answer fully all questions. A copy of the information sheet will be given to the subject.

Written, informed consent will be obtained from each subject by the investigator prior to enrolment in the study. The consent form will be signed and dated by the subject and the investigator. The consent form will be completed in three copies: the first copy is kept in the investigator’s file, the second is kept in the subject’s notes, and the third is given to the participant.

No subject will receive treatment before completion of the written informed consent.

### Ethics committee approval

The study protocol will be submitted by the investigator for examination to the Institutional Ethics Committee (IEC). Commencement of the clinical trial is not permitted without written approval of the ethics committee.

The IEC must be notified of all subsequent additions or changes in the study protocol. Notification of the IEC is also required in the event of a SAE during the clinical trial.

### Declaration of Helsinki

This trial will be conducted according to the principles and rules laid down in the Declaration of Helsinki (Appendix 6) and its subsequent amendments.

# Quality assurance

## 12.1 GCP (Good Clinical Practice)

This clinical trial will be conducted following the principles of ICH (International Conference on Harmonization) guideline for Good Clinical Practice and adherence with the applicable regulatory or legal requirements.

## 12.2 Internal quality control

The clinical trial will be conducted according to GCP and Standard Operating Procedures (SOPs) of the Brain Sciences Institute, Swinburne University of Technology, as well as the SOPs of the Nestlé Research Center, Lausanne, Switzerland.

# Agreements

## 13.1 Monitoring

Regular monitoring visits by representatives of the sponsor will be made during the study.

Monitoring will begin with an initial visit prior to study commencement, or shortly after commencement, to clarify all aspects of the protocol and documentation. The purpose of later visits during the implementation period will be to evaluate study progress and adherence to protocol. The CRA/monitor will check CRFs for completeness, clarity and consistency with the information in patients files (source data checking). At the end of the trial the CRA/monitor will make a study closing visit to all sites to ensure that all documentation is complete. In all cases, it is the responsibility of the CRA/monitor to maintain patient confidentiality.

## 13.2 Responsibilities of investigator

The investigators are responsible for the following:

- Obtaining the written and dated approval of the local ethics committee (and other local regulatory agency, if any) prior to the beginning the study
- Selection of participants in accordance with the inclusion and exclusion criteria; obtaining the informed consent of the subject or legal guardian
- Maintain confidentiality of subjects and potential subjects in accordance with the Declaration of Helsinki
- Adherence to the study protocol and the spirit of Good Clinical Practice. If modification becomes necessary, the rationale will be provided in a protocol amendment signed by the investigator and sponsor for submission to the ethics committee.
- Accurate and complete data collection
- During the course of the trial, provide subjects with any newly available information which may be relevant to them
- Identification of adverse events with notification to sponsor, ethics committee and health authorities, as applicable
- Co-operation with monitoring visits, audits and regulatory inspections. Providing direct access to source data and documents
- Investigator may select a second contact at their study center to assist in implementation of the study. However, in all cases the main responsibility with respect to all aspects of this implementation rest with the principal and co-investigators.
- Archiving of the Investigator’s file (including the original signed informed consent forms of all patients) for at least 10 years after the end or the termination of the trial.

## 13.3 Responsibilities of sponsor

The sponsor is responsible for the following:

- Preparation of study products under Good Manufacturing Practice (GMP)
- Product labelling to maintain blinding/masking per protocol
- Delivery of study products to study site with maintenance of records of product shipments
- Distribution of study protocol, case report forms, dietary records and sample collection supplies *(as appropriate)* to clinical sites
- Adherence to study protocol. If modification becomes necessary, the rationale will be provided in a protocol amendment which will be signed by both investigator and sponsor.
- Regular study monitoring
- Obtaining insurance protection
- Archiving of the Study Master File (including the original case report forms) for at least 5 years beyond the expiration date of the last batch.

## 13.4 Termination of study

The study, once commenced, can only be terminated in accordance with Article 15 of the Clinical Trial Agreement between Swinburne and Nestec. Should it prove necessary to discontinue the study permanently prior to completion the sponsors will notify the investigators and additional contacts, including the IRB/IEC, of the rationale. All study relevant documents will then be returned to the sponsor, and the study product will be destroyed or returned.

# Appendices

| Appendix 1 | Treatment Labels |
| --- | --- |
| Appendix 2 | List of foods to avoid 24 hours prior to experimental sessions |
| Appendix 3 | Mood Visual Analogue Scales |
| Appendix 4 | Flow chart |
| Appendix 5 | Adverse events handling and AE Report Form |
| Appendix 6 | Declaration of Helsinki |

Appendix No 1

tREATMENT LABELS

| **10.09.NRC**  **Instant powder for oral administration**  **Code 1009-A**  **Expire date: ??.2011  Storage: room temperature**  **Quantity: 6g in 300ml water**  *For clinical trial use only, not for sale*  *Produced by PTC Orbe,Switzerland*  *for Nestec Ltd* | **10.09.NRC**  **Instant powder for oral administration**  **Code 1009-B**  **Expire date: ??.2011  Storage: room temperature**  **Quantity: 6g in 300ml water**  *For clinical trial use only, not for sale*  *Produced by PTC Orbe, Switzerland*  *for Nestec Ltd* |
| --- | --- |
| **10.09.NRC**  **Instant powder for oral administration**  **Code 1009-C**  **Expire date: ??.2011  Storage: room temperature**  **Quantity: 6g in 300ml water**  *For clinical trial use only, not for sale*  *Produced by PTC Orbe, Switzerland*  *for Nestec Ltd* |  |

Note: the expiry date will not be known until the CGA is produced.

Appendix No 2

LIST OF FOODS TO AVOID 24 HOURS PRIOR TO EXPERIMENTAL SESSIONS

**Food and drink to be avoided during 24 hours**

**prior to every testing session.**

| **Drinks**  **AVOID:** | **Drinks that are OK** |
| --- | --- |
| **All** types of tea (e.g. earl grey, green, black, Oolong)  Drinks containing tea (ready to be consumed, instant)  Herb teas  Coffee  Hot chocolate/Cacao/Nesquik/Milo | Hot milk |
| Fruit juice, in particular:  Orange juice  Grape juice  Apple juice | Cordial, lemonade, lemon drink, water |
| All alcohol |  |
| **Fruits, vegetables, nuts**  **AVOID:** | **Foods that are OK** |
| Blackberries | Banana |
| Green and red grapes | Melon |
| Raspberries | Pineapple |
| Strawberries | Pear |
| Blueberries | Carrot |
| Cherries | Pasta |
| **All** citrus fruit such as oranges, grapefruit, lemon, lime, tangerines | Rice |
| Plums |  |
| Apples |  |
| Raisons, Currants |  |
| Olives |  |
| Spinach |  |
| Asparagus |  |
| **All** Nuts, e.g. hazelnuts, walnuts, almonds, peanuts, etc |  |
| **Cereals and Breads**  **AVOID:** | **Foods that are OK** |
| Buckwheat | Cereals containing rice |
| Oats | White bread |
| Barley |
| Corn/Wheat |
| Broad beans |
| Lentils |  |
| **Desserts, sweets, biscuits**  **AVOID:** | **Foods that are OK** |
| Anything containing chocolate e.g. chocolate bars, chocolate, cakes, chocolate biscuits, chocolate cream, chocolate mousse, chocolate ice-cream | Plain yogurt |
| Cereal bars | Honey |
| Jams and frozen fruits |  |
| Nutella |  |
| **Other**  **AVOID:** | **Foods that are OK** |
| Olive oil | Vegetable oil |
| Grape oil |  |

Appendix No 3

MOOD VISUAL ANALOGUE SCALES

Appendix No 4

FLOW CHART

**V0**

**V1**

**V2**

1 week

1 week

1 week

**V3**

Wash-out

Wash-out

Wash-out

**Training session**

**Blood sample**

**Mood scales**

**Cognitive test**

**Doppler blood flow**

**Blood sample**

**Mood scales**

**Cognitive test**

**Doppler blood flow**

**Blood sample**

**Mood scales**

**Cognitive test**

**Blood sample**

Experimental session for V 1, 2, and 3

Breakfast

Mood

Cognition

Tx

Mood

Mood

Cognition

Blood Doppler

Mood

Cognition

Blood

Finish

Mood

Blood

Mood

0

15

17

57

70

95

125

128

173

205

207

250

252

265

175

Doppler

60

Appendix No 5

ADVERSE EVENTS (AE) HANDLING & AE REPORT FORM

